**Figure 5: BRIDGE Site Selection Process**

[figure not shown]

[figure not shown]

24 study sites

From the mapping data we collected for this project (conducted under separate IRB protocols AAAQ8761 and AAAQ6156), and by consultation by the Republican AIDS Center the following criteria were determined and will be applied in this trail:

Criterion #1: Trust point must be located within 20km of AIDS Center

This eligibility criterion is important given the large barrier that transportation plays in accessing care. If a trust point is located very far from an AIDS Center, it represents an additional unnecessary barrier to accessing services.

- In Almaty, 1 potential trust point was excluded for not meeting this criterion
- In Shymkent, 8 potential trust points were excluded for not meeting this criterion
- In Karaganda/Temirtau, 3 potential trust points were excluded for not meeting this criterion

Criterion #2: Rapid HIV testing is an existing part of current TP services

Rapid HIV testing must be currently performed in the physical location of the TP (by full-time nurse or staff or by visiting nurse/doctor). If a trust point does not currently perform rapid testing, we will not have adequate pre-intervention data to compare

In Almaty, 2 trust points do not meet this criterion because they do not currently have medical staff – NOT excluded, because they are likely to hire such staff

In Karaganda, 1 trust point does not meet this criterion

Criterion #3: Physical infrastructure of TP: Separate room available for private counselling & testing

Since HIV rapid testing and ARTAS activities require a private space, we have excluded all polyclinics that do not have a room for private consultation with clients. This is based on question from mapping surveys: How many rooms do you have available for private consultations with clients? TPs must report at least one to be included.

In Karaganda, 1 trust point does not meet this criterion

In Shymkent, 1 trust point does not meet this criterion

Criterion #4: Trust point is located in a region which has higher numbers of injection drug users

Prevalence of injection drug use is determined by GHRCCA staff in consultation with the local AIDS Center and Narcology departments. GHRCCA staff makes decisions based on neighborhood characteristics: removed trust points who don't have high prevalence of PWID in the neighborhood.

\*\*Note that this is NOT necessarily based on the numbers of PWID that each trust point reported serving in the mapping surveys, since we are interested in potential recruits, and not a high number of PWID who are already linked to care.

\*\*In Almaty, the trust points have been ranked in order of highest prevalence of PWID in the neighborhood, the top 8 (who meet eligibility criterion 1,2,3, and 5) are selected for inclusion.

Criterion #5: Trust point staff and/or leadership are unwilling to participate in project

All Trust Point sites are regulated by the RAC; therefore we have access to all the TPs and full support from the Director of RAC. However, in the event that a trust point does not wish to participate in the BRIDGE study, we cannot enforce their participation and this TP will not be included. There are many factors that may determine a trust point's willingness to participate (pressure from AIDS Center, more information about the project, staff availability), and the BRIDGE study team will be limited by this.

Of the selected 24 TP sites, about 20% will be AIDS Center TP sites operated by the Republican AIDS Center, 60% will be TP sites located and operated by public polyclinics (primary care clinics), and 20% will be independent NGO sites.

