#### 3.2. RELATIONSHIPS WITH LOCAL PARTNERS IN EACH CITY

As an implementation science study, BRIDGE is deeply dependent on local health service organizations and

oversight bodies for both project implementation and data collection. The thorough needs assessment process during the first year of the study, which included both mapping surveys and focus groups with PWID, provided the research team with an understanding of the system of HIV care in each of the four study sites where BRIDGE will be implemented. BRIDGE staff will work with local partners in both a formal capacity (through service contracts), and an informal advisory capacity.

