### 3.7. TRUST POINT ELIGIBILITY CRITERIA & SELECTION

Bridge will be carried out at a total of 24 trust points, or 8 per site (3 from Temirtau and 5 from Karaganda will be considered one site). A selection process within each site will identify the “BRIDGE Trust Points” who will carry out the intervention, and the “non-BRIDGE Trust Points” where no intervention will take place.

A multistage site selection process was carried out according to Figure 5:

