### Post-Implementation Survey

Following the start of the intervention in each city, the nurse will administer a post-implementation survey on an electronic tablet to every client who comes to the trust point or AIDS Center. The Post-Implementation survey will contain questions regarding which services were administered to the client, including, in the Trust Point Nurse surveys, the BRIDGE intervention components of SNS recruitment (whether the client was referred as part of the peer recruitment strategy) and ARTAS (whether the client completed an ARTAS session during that visit). No personally identifiable information will be collected. Responses will be linked to a unique study ID number for each client. The Post-Implementation Survey will take approximately 5 minutes to complete.

Study sites will switch from the pre-implementation to the post-implementation survey once BRIDGE is rolled out in their city. Due to the stepped-wedge design of BRIDGE, each study site will make this switch at a different time. A graphic is provided below, where month 13 (the start of data collection) is November 2016.

[figure not shown]

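### Section 3.7 waives the on-site testing criterion for two Almaty trust points and then says the selected Almaty trust points meet it; if the two are among the 24, the testing comparison cannot separate new test availability from BRIDGE

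*Combined protocol and SAP*

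**What the plan says.** Section 3.7 fixes the number of clusters: "Bridge will be carried out at a total of 24 trust points, or 8 per site". Criterion #2 states the rule, "Rapid HIV testing must be currently performed in the physical location of the TP", which a visiting nurse or doctor may satisfy. It also gives the reason: "If a trust point does not currently perform rapid testing, we will not have adequate pre-intervention data to compare".

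The same criterion then records an exception. "In Almaty, 2 trust points do not meet this criterion because they do not currently have medical staff", and these two are "NOT excluded, because they are likely to hire such staff". No hiring date, deadline or fallback is given. One Karaganda TP is also listed as failing the criterion; what happened to it is not stated.

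The note under Criterion #4 describes the final Almaty step. TPs are ranked by neighbourhood prevalence of injection drug use, and "the top 8 (who meet eligibility criterion 1,2,3, and 5) are selected for inclusion".

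The number of PWID tested at TPs is among the primary outcomes under Aim 1 (Section 1.2) and is hypothesis (b) of the Data Analysis Plan for Primary Study Aim, although Section 2.4 and Appendix A place testing under Aim 2. The permutation test in Section 2.4 and in the Data Analysis Plan uses the difference in means between implementation and pre-implementation periods. The mixed-model and GEE text names no term for staffing or test availability. There is no rule for when a TP's data become evaluable and no sensitivity analysis without particular TPs.

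**The concern.** The exception removes the protection that the criterion was written to give. A TP with no one to test can show no tests in its early quarters and some tests once a nurse is in post, whether or not BRIDGE does anything. Such a step at two TPs lies inside one of only three randomised sites. If it falls near that site's rollout, it looks like an intervention effect on tests at TPs.

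Hiring near rollout is plausible. BRIDGE relies on TP nurses to test, and Sections 4 and 9 schedule nurse training one month before rollout. The service contracts that cover hiring of TP nursing staff (Section 3.2) are planned for Shymkent and Karaganda but not for Almaty, so the documents describe no study control over the timing there.

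**Working it through.** **Plan's own figures.** 3 sites × 8 TPs = 24, as stated. The 80% power figure cannot be reproduced because the effect size and ICC are not in the text; nothing below depends on it.

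**Inputs from the documents**
- The needs assessment, including mapping, was in study year 1 (Section 3.2: "The thorough needs assessment process during the first year of the study, which included both mapping surveys and focus groups with PWID").
- Outcome data start in month 13 (Appendix A: "where month 13 (the start of data collection) is November 2016").
- Rollout is in months 22, 28 and 34 (Section 2.2). Almaty's position is random and not given.
- Measures are quarterly over 42 months (Section 2.4): 42/3 = 14 quarters.
- Pre-period lengths: (22 − 13)/3 = 3, (28 − 13)/3 = 5 and (34 − 13)/3 = 7 quarters.
- Pre-period TP-quarters: 8 × (3 + 5 + 7) = 120. Implementation TP-quarters: 24 × 14 − 120 = 216.

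**Assumptions (not in the documents).** Every staffed TP tests the same volume m per quarter, an unstaffed TP records zero, BRIDGE has no true effect, and both TPs are among the 24.

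**Formula.** Let the two TPs be at zero for the first h quarters and let L be Almaty's pre-period length. For h ≤ L:
- pooled spurious change = 1/(1 − 2h/120) − 1
- Almaty-only spurious change = 1/(1 − 2h/(8L)) − 1

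For h > L, the pooled numerator becomes 1 − 2(h − L)/216 and the denominator uses h = L.

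**Zero for the whole pre-period, staffed at rollout (h = L)**
- Almaty only: 1/(1 − 2/8) − 1 = 8/6 − 1 = +33.3% in every order.
- Pooled, Almaty first: 1/(1 − 6/120) − 1 = +5.3%.
- Pooled, Almaty second: 1/(1 − 10/120) − 1 = +9.1%.
- Pooled, Almaty third: 1/(1 − 14/120) − 1 = +13.2%.

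**Other hiring dates, pooled**

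| Staffing of the two TPs | Almaty 1st | Almaty 2nd | Almaty 3rd |
|---|---|---|---|
| Before month 13 | 0 | 0 | 0 |
| After one zero quarter | +1.7% | +1.7% | +1.7% |
| Two quarters after rollout | +3.3% | +7.1% | +11.1% |
| Never | −5.5% | 0.0% | +5.9% |

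Example for the third row, Almaty first: (1 − 4/216)/(1 − 6/120) − 1 = +3.3%. For the fourth: (1 − 22/216)/(1 − 6/120) − 1 = −5.5%.

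**Does adjustment for time remove it?** A least-squares fit with TP and quarter effects on the same null data gives, as a percentage of m (Almaty first, second, third):
- hiring at rollout: +5.1, +8.0, +11.9
- hiring within the pre-period (after 1, 2 and 3 quarters): +1.7, 0.0, −5.1
- hiring two quarters after rollout: −7.4, 0.0, +8.5
- never: 0 in each order

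Adjustment leaves most of the bias when hiring coincides with rollout. For other dates the sign depends on Almaty's step.

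**If the quarters are unrecorded rather than zero.** TP nurses assign the AppSheet IDs and complete the surveys, so a TP without a nurse may produce no records. With equal volume, the mean over recorded TP-quarters is then m in both periods and the arithmetic bias is nil. The two TPs would, however, contribute no pre-period for attendance or linkage either. The plan does not say how such quarters would be entered.

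**The case against.** The strongest reply is that these TPs may never enter the comparison unstaffed. The exception sits at one step of a multistage selection. The final Almaty rule takes only TPs that meet criterion 2, so the two may have been ranked out or staffed by then, and the figure that shows the selection flow is not available here. Between mapping in year 1 and the earliest rollout in month 22 there is time to hire, and the AppSheet procedures presume a nurse at each BRIDGE TP from November 2016. This stands: inclusion is unsettled, and any zero lasts only until hiring.

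A reader might infer that the two TPs are definitely kept, that their pre-period testing is zero by construction, and that hiring will be counted as BRIDGE effect. The documents support none of these as fact. Nor do they show that Karaganda was treated more strictly, since its failing TP has neither a reason nor an outcome recorded. It is also tempting to say that hiring after rollout masks the effect. In the unadjusted pooled comparison, hiring two quarters late still inflates it; only the fit with TP and quarter effects, with Almaty first, turns negative.

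Two further points stand. If BRIDGE prompts the hiring, the gain may belong to the intervention; the documents do not say. And a TP without on-site testing need not have zero linkage, because BRIDGE also links known positives who have left care. Tests at TPs are the outcome clearly exposed.

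The reply does not remove the conflict between the two statements, the missing hiring date, or the absence of any analysis that separates test availability from BRIDGE.

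**Conclusion.** The concern holds in conditional form. The exception under Criterion #2 and the Almaty selection rule under Criterion #4 disagree and must be reconciled. If the two TPs are among the 24 and unstaffed when data collection starts, the planned comparison of tests at TPs can be biased by a change in staffing.

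Under the stated assumptions, the size for hiring at rollout is +33% in Almaty and +5.3% to +13.2% pooled. Across the hiring dates examined, the pooled range is −5.5% to +13.2%, with nil if both are staffed before month 13. These figures rest on equal volume per staffed TP and recorded zeros. They illustrate possible size and do not forecast it. Because the direction depends on a hiring date and a randomised order that the documents do not give, a rule set in advance is the appropriate response.

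**What to change.** 1. Reconcile the two statements in Section 3.7, say whether the two Almaty TPs are among the 24, and state what became of the Karaganda TP that failed the same criterion.
2. Apply criterion #2 as of the start of data collection (month 13). If either Almaty TP still does not test on site, take the next-ranked Almaty TP that meets criteria 1, 2, 3 and 5, where one is available. The documents do not give the length of the ranked list.
3. If none is available, keep the two TPs. Record each TP's first date of on-site testing, and state whether quarters before that date are entered as zero or missing.
4. Pre-specify two sensitivity analyses of the testing outcome: (i) omitting TP-quarters before testing was available, and (ii) omitting the two TPs, which leaves 22.
5. Do not drop TPs from the primary comparison because hiring came after rollout. That would condition on an event BRIDGE may itself have influenced.

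The cost is a swap of two TPs, or one extra date per TP and slightly fewer TP-quarters in the sensitivity analyses. The primary analysis keeps 24 TPs.

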### 3.8. PARTICIPANTS

#### Categories of Participants for this study

There are three categories of participants in this implementation study:

- 1) PWID Program Participants: - All PWID (regardless of HIV status) in each of the four cities are considered participants in terms of program-level outcomes of BRIDGE. These clients are eligible to receive various components of the BRIDGE intervention: they may be recruited by peer recruiters as part of the SNS strategy or may be peer recruiters themselves, they will receive CTR at trust points, and those who are HIV-positive are eligible to participate in ARTAS.

#### Compensation (by category of participants listed above)

- 1) PWID program participants in the four cities receive no compensation for taking part in BRIDGE activities, as this is an implementation study. BRIDGE is designed to for trust points to provide it under their normal scope of activities. The one exception is peer recruitment: PWID who become BRIDGE peer recruiters will receive \$2 compensation for every participant successfully referred to the trust point for HIV rapid testing (up to a maximum of \$40), and an additional \$2 for filling out a brief survey when they initially register their coupon numbers with the trust point nurse. This compensation will be provided and monitored by the local project team, but distributed by the trust point nurses. No incentives are given for testing or participation in the study intervention ARTAS sessions.

### 3.9 QUALITY ASSURANCE

Process Measures completed during BRIDGE Implementation: To evaluate the extent and fidelity of BRIDGE intervention implementation, the study will employ a number of process and quality assurance measures. We will develop a number of monitoring forms for trust point staff (nurses and outreach workers) to complete as they perform different parts of the intervention. Local site coordinators will be responsible for monitoring this feedback, and, together with the project director, conducting regular quality assurance checks. All process and quality assurance measures are listed in the chart below:

| Table 3: Study Process and Quality Assurance Measures  |                                                        |             |                                           |
|--------------------------------------------------------|--------------------------------------------------------|-------------|-------------------------------------------|
| Variable                                               | Measures                                               | Time points | Source                                    |
| Staff time conducting BRIDGE                           | Staff timesheets/logs                                  | Weekly      | TP staff (monitored by site coordinator)  |
| Staff trained in SNS, CTR, ARTAS                       | # staff trainings; training attendance logs            | Monthly     | Project director, site coordinator        |
| BRIDGE training quality                                | # training evaluations, and satisfaction surveys       | Monthly     | TP staff, (monitored by project director) |
| SNS training sessions held with peer recruiters        | # coaching sessions; staff SNS log                     | Monthly     | TP staff (monitored by site coordinator)  |
| Quality of SNS training for peer recruiters            | SNS fidelity forms                                     | Ongoing     | TP staff (monitored by site coordinator)  |
| Network associates referred to trust point through SNS | SNS Coupon Tracking Form                               | Ongoing     | TP staff (monitored by site coordinator)  |
| CTR HIV Rapid Tests completed                          | Staff rapid testing logs & rapid testing fidelity form | Ongoing     | TP staff (monitored by site coordinator)  |

|                                                             |                                                                                                              |                             |                                          |
|-------------------------------------------------------------|--------------------------------------------------------------------------------------------------------------|-----------------------------|------------------------------------------|
| ARTAS Enrollment & Session Completion                       | # ARTAS clients assigned, ARTAS sessions conducted with session log; vouchers completed                      | Ongoing                     | TP staff (monitored by site coordinator) |
| ARTAS Session Adherence Form                                | ARTAS fidelity form                                                                                          | Ongoing, ARTAS Sessions 1-5 | TP ARTAS Staff                           |
| BRIDGE quality assurance and client coordination maintained | Attendance of TP staff at biweekly supervision meetings and number and type of technical assistance episodes | Bi-weekly                   | TP Nurse and Staff                       |
| BRIDGE Client Satisfaction and Peer Norms about Services    | 17-item client satisfaction questionnaire to assess attitudes towards TP services and BRIDGE                 | Ongoing                     | TP Clients (administered by TP staff)    |

#### 4. STAFF SELECTION AND TRAINING

Each BRIDGE study site will consist of a site coordinator to oversee all site activities, 8-16 nurses/social workers implementing ARTAS and 8-16 outreach workers conducting SNS recruiting. In addition, AIDS Center staff will be trained on AppSheet Data collection. Please see the organizational chart in Appendix D for a complete description of staff structure.

##### *General Training*

All study staff will undergo a common training that covers: (1) ethical issues in research; (2) establishing and maintaining rapport with participants; (3) obtaining informed consent; (4) addressing participants' concerns with confidentiality and handling sensitive situations; (5) obtaining accurate tracking information; (6) managing distress and conducting crisis and enhanced referrals; and (7) detecting, handling, and reporting adverse events.

##### *Training and Supervision of Data Collection Staff*

Recruiters will receive an additional 25 hours of standardized training regarding data collection.

##### *Training and Supervision of BRIDGE Intervention staff*

We will provide a 7-day training for TP outreach workers, social workers and nursing staff who will implement and oversee integrated BRIDGE components in each city one month prior to BRIDGE rollout. New staff will be invited to attend subsequent trainings in other cities or make-up trainings with BRIDGE staff. To build local capacity and further integrate the BRIDGE program into the existing TP and AIDS Center system, we have identified (with the help of Trust Point and AIDS Center leadership) a local supervisor at each study site who will take primary responsibility for all supervision, with technical and program assistance from the GHRCCA and CU study teams as necessary. This supervisor will be responsible for monthly monitoring of trust point nurses, for facilitating a monthly staff meeting (known as the community of practice) where all BRIDGE implementation staff will share their experiences and learn from each other, and by monitoring a text messaging group where these same staff can share ongoing concerns. As with all BRIDGE intervention activities, these supervision protocols have been created to align with local supervision protocols. We have developed structured manuals and implementation protocols for all BRIDGE program and supervision activities. The Study Project Director will be available to provide technical assistance to supervising nurses. Data on number and type of technical assistance contacts will be collected for Aim 4.

#### 5. STUDY SUBJECTS

According to the Republican AIDS Center, there were an estimated total of 25,394 PWID in the 4 cities with an average of 597 registered PWID clients per TP in 2014. The 24 TP study sites should yield a pool of potential 14,328 PWID participants of whom it is estimated 13.3% on average will test positive for HIV ( $n=1,891$ ) based on RAC surveillance reports of HIV prevalence rates in the 4 cities. This existing pool of potential TP registered clients in addition to new PWID clients recruited during the two year enrollment period should be adequate to assess

program outcomes for Aim 1 and Aim 2 outcomes.

*Gender and Minority Inclusion:* We anticipate that 80% of the PWID and TP staff and nurses will identify as Asian, 30% of PWID will be women, and 50% of the TP staff and HIV Care Center nurses will be women.

*Participation of Children:* The study will include women and men aged 18 or over, including youth 18 to 20 years of age. Younger children will be excluded because the BRIDGE intervention has not been designed for them and they are not currently served by TP. The investigative team includes certified social workers who are trained to work with young adults aged 18 to 20 years.

